#### Secondary outcomes

The following are the secondary outcomes:
Heart rates variability, based on routine 24-h BP monitoringAssessment of any improvement in TCM Syndrome, using TCM Syndrome Integral Scale (Additional file 2). In this scale, the score of the symptom will be based on the severity, duration, and frequency of the symptoms: 0 points means the symptom did not appear in the past 1 month, 1 point means the symptoms are mild or the frequency of attacks is low, 2 points means the symptoms are moderate or the frequency of attacks is moderate; and 3 points means the symptoms are very severe or the symptoms constantly puzzled. The TCM therapeutic effect Index (TCMTEI), as calculated with the following formula, will be used to evaluate the treatment efficacy in the TCM syndrome.
$$ \mathrm{TCMTEI}=\left(\frac{\mathrm{symptom}\ \mathrm{score}\ \mathrm{before}\ \mathrm{treatment}-\mathrm{symptom}\ \mathrm{score}\ \mathrm{after}\ \mathrm{treatment}\ }{\mathrm{symptom}\ \mathrm{score}\ \mathrm{before}\ \mathrm{treatment}}\right)\times 100\% $$Assessment of any improvement in quality of life, using the 36-Item Short Form Health Survey [50, 51].Changes in levels of blood lipids, including total cholesterol, triglycerides, low-density lipoproteins, and high-density lipoprotein.Serum pro-inflammatory/anti-inflammatory cytokines in patients: changes in the serum levels of TNFα, IL2R, IL6, IL8, IL10, and IL1β will be assessed at baseline and treatment endpoint.Pharmacogenomic evaluation: twenty loci/SNPs associated with BP/hypertension will be assessed at baseline and treatment endpoint.Safety evaluation: routine blood and urine test including levels of creatinine, blood glucose, and homocysteine will be assessed at baseline and treatment endpoint.

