## Methods and design

### Objectives

Our study aims to assess the clinical effect of BSJY on pharmacogenomics and pro-inflammatory/anti-inflammatory cytokines in patients with low-to-medium-risk hypertension, to firstly provide a preliminary pharmacogenomic evaluation of antihypertensive responses in hypertension, and to observe whether TCM plus Western medicine has a better curative effect than Western medicine alone.

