**Effectiveness observation**							
Blood pressure	√		√	√	√	√	√
24-h blood pressure			√				√
Pro-inflammatory/anti-inflammatory cytokines			√				√
Improvement in TCM syndrome			√	√	√	√	√
Improvement in quality of life			√				√
Pharmacogenomic evaluation			√				√

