### Statistical analysis

#### Sample size calculation

The formula used to calculate the sample size is as follows, which is based on superiority clinical trial interval hypothesis test sample size estimation [52]. The sample size was calculated based on the expected reduction in reducing of BP. One previous study suggested that the reduction of BP after interventional treatment is 4.5 mmHg, and the BP SD is 10 mmHg. Therefore, we assume the reduction of BP as 4.5 mmHg in this study. In the following formula, *c* is the ratio between two sample cases, *n*1 = *n*2, so *c* = 1. *σ* is the BP SD 10 mmHg, and *δ* is the expected effect BP 4.5 mmHg, so *σ* = 10 and *δ* = 4.5. Given a type I error rate of *α* = 0.05, a power of 90% (type II error rate of *β* = 0.1), so *uα* = 1.96, *uβ* = 1.282. *n1* = *n2* ≈ 104, the sample size for one group needs to be 104, resulting in *n* = 2 × 104 = 208 patients. Considering the maximum possible dropout rate is 20%, a total of 260 patients needs to be allocated to reach the required number of patients for the efficacy analysis.
$$ {\displaystyle \begin{array}{c}{n}_1={\left[\frac{\left( u\alpha + u\beta \right)\sigma }{\delta}\right]}^2\frac{\left(1+c\right)}{c},{n}_2=c{n}_1\\ {}{n}_1={n}_2\approx 104\end{array}} $$

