Pharmacogenomic evaluation of antihypertensive responses offers the clinical promise of individualization of therapy based on a person’s genetic makeup [11]. It is said that the loci/SNPs associated with BP/hypertension are also associated with BP response to antihypertensive drugs [10]. This is the first paper that researches pharmacogenomic evaluation of antihypertensive responses in TCM. The present study is designed as a double-blind, randomized, placebo-controlled trial that will provide high-powered evidence regarding the efficacy, safety, and pharmacogenomic evaluation of BSJY in treating patients with low-to-medium risk hypertension. The progress and quality of the trial will be monitored by a clinical research organization of Guang’anmen Hospital.

There are also some limitations to this study. First, we supposed to test twenty single nucleotide polymorphisms (SNPs) that have been associated with BP in genome-wide association studies in Asian people. It is different that significant genetic loci for BP and hypertension reported in genome-wide association studies in Europeans, Asians, and Africans. It should be considered that the complexity of the genetic mechanisms underlying hypertension and the need for much larger sample sizes when looking for genes associated with BP. For TCM, it can be viewed as a very important environment element to pharmacogenomic evaluation. Second, our multi-center experiments will be conducted in China in the future.

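### The twenty SNPs are scheduled again at week 8 although genotype cannot respond to treatment, and the claim of high-powered pharmacogenomic evidence has no basis in the sample size

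*Protocol article*

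**What the plan says.** The Objectives section of the protocol article sets out to "assess the clinical effect of BSJY on pharmacogenomics" and, in the same sentence, calls the pharmacogenomic evaluation of antihypertensive response preliminary. Under Secondary outcomes, "twenty loci/SNPs associated with BP/hypertension will be assessed at baseline and treatment endpoint". In Table 2 the row "Pharmacogenomic evaluation" is ticked at day 0 and week 8, the same pattern as cytokines and quality of life.

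On size, the Sample size calculation section says: "The sample size was calculated based on the expected reduction in reducing of BP". Its inputs are a 4.5 mmHg effect ("we assume the reduction of BP as 4.5 mmHg in this study") and an SD of 10 mmHg ("the BP SD is 10 mmHg"). It has no genetic input.

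The Discussion says that the trial will give "high-powered evidence regarding the efficacy, safety, and pharmacogenomic evaluation of BSJY". Its limitations paragraph then cites "the need for much larger sample sizes when looking for genes associated with BP". The Strengths and limitations section makes the same concession.

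**The concern.** Two statements do not fit the design.

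The first is timing. A SNP genotype is inherited. If it is read at day 0 and again at week 8, the two readings agree unless there was an assay or sample-handling error. The second reading therefore cannot show anything about BSJY. The wording of the objective, an effect of the granule on pharmacogenomics, points the same wrong way: it makes genotype a response. The Introduction and Discussion describe something else, namely loci that are associated with the BP response to antihypertensive drugs. There genotype is a fixed predictor or modifier, and the BP change is the response.

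The second is the power claim. It extends to the pharmacogenomic evaluation, although the trial was sized for the overall BP difference alone. Pharmacogenomics is in the trial's title, so readers may give a positive or a null genetic result more weight than the design can bear.

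**Working it through.** **Step 1. Timing.** The Secondary outcomes text and Table 2 agree on day 0 and week 8, so this is not a slip in one place. No section names a marker that could change between the visits. Table 2 also schedules 24-h BP at day 0 and week 8, so the response that genotype could be related to is collected.

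**Step 2. Reproduce the plan's own sample size.** Inputs from the Sample size calculation section: σ = 10, δ = 4.5, u_α = 1.96, u_β = 1.282, c = 1, dropout 20%.

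n per group = 2 × [(1.96 + 1.282) × 10 / 4.5]² = 103.8, rounded up to 104. Total 208; 208 / 0.8 = 260.

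The stated figures reproduce, with about 90% power, for the between-group BP difference only.

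**Step 3. Illustrative power for one SNP as modifier of the treatment effect.** From the document: 104 evaluable per arm, SD 10. Assumed, because the document gives neither: carrier share f from 0.1 to 0.5, and an interaction D of 4.5 mmHg (carriers and non-carriers differ in treatment effect by as much as the whole assumed effect).

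SE = 10 × √[(2/104) × (1/f + 1/(1 − f))]; power = Φ(D/SE − z).

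For f = 0.5: SE = 10 × √(0.01923 × 4) = 2.77, and D/SE = 1.622.
- Two-sided 0.05: Φ(1.622 − 1.960) = 0.37
- One-sided 0.05: Φ(1.622 − 1.645) = 0.49
- Two-sided 0.05/20 = 0.0025: Φ(1.622 − 3.023) = 0.08

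| Carrier share | SE (mmHg) | Two-sided 0.05 | One-sided 0.05 | Two-sided 0.0025 |
|---|---|---|---|---|
| 0.5 | 2.77 | 37% | 49% | 8% |
| 0.3 | 3.03 | 32% | 44% | 6% |
| 0.2 | 3.47 | 25% | 36% | 4% |
| 0.1 | 4.62 | 16% | 25% | 2% |

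The one-sided column is shown because the Planned data analysis section calls all tests one-sided, while the sample size uses 1.96. A share of 0.5 is the most favourable, since 1/f + 1/(1 − f) is smallest there. With all 260 evaluable and f = 0.5, two-sided power is 44% at 0.05 and 11% at 0.0025.

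**Step 4. What 90% power would need for D = 4.5.** Total N = 4 × (1/f + 1/(1 − f)) × [10 × (1.96 + 1.282)/4.5]². This is 831 evaluable at f = 0.5 and 2307 at f = 0.1, unadjusted.

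**Step 5. A weaker target.** If the aim were only an association of genotype with BP change, pooled over arms, SE = 10 × √[(1/208) × (1/f + 1/(1 − f))], half the interaction SE. For a 4.5 mmHg carrier difference, D/SE is then 3.245 at f = 0.5 and 1.947 at f = 0.1. Two-sided power is 90% and 50% at 0.05, and 59% and 14% at 0.0025. Both arms take amlodipine, so a pooled association does not isolate a response to BSJY.

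**The case against.** The strongest reply is that the harm is small and partly admitted. The timing phrase also appears for cytokines and safety tests, and may be template wording. The article concedes twice that genetic questions need much larger samples and calls the evaluation preliminary. The high-powered claim is one Discussion sentence. The document never states a genotype-by-treatment interaction, and carrier share and interaction size are not in it. Much of this stands: the power problem is a contradiction in wording and not a hidden gap, and the figures are illustrations. It does not give the week-8 SNP reading a purpose, nor does it support the power claim.

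Three stronger readings are tempting, and the documents do not support them.
- A reader might infer that the pharmacogenomic question cannot be answered. Baseline genotype and 24-h BP at both visits are scheduled, so it can still be studied.
- A reader might infer that a change in SNPs will be analysed. The outcome list speaks of changes for lipids and cytokines but not for SNPs; it only says when they are assessed.
- A reader might infer that no interaction model or multiplicity control is planned, so that unadjusted tests will produce false positives. A statistical analysis plan that is not shown may contain both. The 0.05/20 column is a reference point and not a claim about what is missing.

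**Conclusion.** The point holds in two limited parts. The week-8 SNP assessment is uninformative about BSJY as written, and the objective wrongly treats genotype as something that treatment affects. This rests only on genotype being fixed and on no changeable marker being named.

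The high-powered claim for pharmacogenomics is unsupported by the sample size and conflicts with the article's own limitation. Under the stated assumptions, an interaction as large as the whole assumed treatment effect has at best 37% power two-sided or 49% one-sided per SNP with 208 evaluable, and 8% or less at 0.05/20. Larger interactions fare better: one of about 9 mmHg, twice the assumed overall effect, reaches 90% at two-sided 0.05 with half the patients carriers. The outcome is secondary and the primary BP comparison is untouched. It should be corrected, but it does not threaten the trial's main result.

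**What to change.** Genotype once, at baseline, and delete the week-8 tick in Table 2 and the matching words under Secondary outcomes. If expression, methylation or another changeable marker was meant, name it instead.

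Restate the objective and outcome as the relation of baseline genotype at the twenty loci to the change in 24-h BP, including whether genotype modifies the treatment effect. Label it exploratory, in line with the preliminary status already given in Objectives. In the Discussion, limit the power claim to the BP comparison for which the trial was sized.

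The cost is a change of wording, one schedule tick and a less ambitious claim. If a separate week-8 assay is run, up to 260 repeats would be saved, fewer for patients already finished (80 at manuscript submission); the document gives no laboratory detail to confirm this. The Trial status section reports continuing recruitment and no analysis, so on that account the change can precede any results.

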### Data collection and management

The case report form (CRF) will be used for recording the process for each participant. In addition to the enrollment evaluation (− 7 ± 0 days), each participant will attend an evaluation visit when allocated and every 2 weeks afterwards during the trial (0 days, 2 weeks, 4 weeks, 6 weeks, and 8 weeks). The assessments including physical examination, improvement in symptoms, compliance with medications, questions about adverse events will be given to each participant. Blood tests and 24-h BP monitoring will be evaluated only at the enrollment and close-out visits. The schedule of enrollment, interventions, and assessments can be checked in Table 2. All researchers involved in data entry and data management will sign a confidentiality agreement to prevent data leakage. The personal information of all participants will be carefully protected, and the original CRF will be kept for 5 years after the end of the trial.

**Table 2 Tab2:** Schedule of the data collection

Process/item	Run-in period	Run-in period	Pre-treatment	Treatment period			
Time point	− 7 day	− 1 day	0 days	2 weeks	4 weeks	6 weeks	8 weeks

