#### Exclusion criteria

The exclusion criteria include the following: uncooperative patient; secondary hypertension (symptomatic hypertension); severe hypertension systolic BP ≥ 180 mmHg and/or diastolic BP ≥ 110 mmHg; severe heart failure; insulin-dependent diabetes; infectious diseases; hyperthyroidism, combined with severe primary diseases including liver, kidney, hematopoietic system, nervous system, mental illness, and malignant tumors; patients participating in other clinical trials; pregnant or breastfeeding women; and with recent history of trauma.

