**Baseline information**							
Informed consent	√						
Eligibility screen			√				
Medical history	√						
Allocation	√						

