**Safety observation**							
Physical exam		√					√
Blood pressure		√					√
Routine blood test		√					√
Routine urine test		√					√
Liver and kidney function		√					√
Adverse event				√	√	√	√

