#### Planned data analysis

The intention-to-treat principle will be used to analyze the efficacy and safety of BSJY. The independent data administrator and the professional statistician will undertake data entry and data management, and perform the data analysis, respectively. All the efficacy and safety analyses with all randomly assigned participants included will be conducted within the full analysis set (FAS). The per-protocol set (PPS) analysis will also be conducted to compare the results from FAS and PPS. Demographic and laboratory characteristics will be calculated at baseline and after the treatment period for all patients. The statistical analysis will be done at Guang’anmen Hospital, China Academy of Chinese Medical Sciences in Beijing.

For continuous variables with normal distribution, the comparability of the characteristics between the two study groups will be assessed by using the *t*-test. While for the comparison of data with non-normal distribution, the non-parametric Mann-Whitney-Wilcoxon test will be used. Continuous variables will be expressed by mean ± SD. We will assess the paired *t*-test to compare the difference of the outcome between preintervention and postintervention in each group by using the independent *t*-test. A *χ*^2^ test will be used for categorical variables, while the Fisher exact test will be used when the theoretical frequency is less than 5 in more than 25% of the cells. Categorical variables will be shown as counts and percentages. Whether the hypothesis of superiority is available will be judged by comparing the 95%CI of the difference in intergroup efficacy. All statistical tests are unilateral tests; *p* < 0.05 is statistically significant. All statistical analyses will be performed using SPSS V.20.0.

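### Table 2 allocates participants at day -7, seven days before the eligibility screen and the baseline 24-h BP, while the text places allocation at day 0

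*Protocol article*

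**What the plan says.** The text of the Protocol article (Data collection and management) sets an enrollment evaluation at day -7. In addition to it, each participant has an "evaluation visit when allocated and every 2 weeks afterwards during the trial (0 days, 2 weeks, 4 weeks, 6 weeks, and 8 weeks"). Allocation therefore belongs to the first visit of that list, day 0. The same paragraph refers the reader to Table 2 for the schedule.

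In Table 2, Allocation is ticked once, at day -7, beside informed consent and medical history. The row "Eligibility screen" is ticked once, at day 0. The row "24-h blood pressure" is ticked at day 0 and week 8. The rows "Routine blood test" and "Liver and kidney function", under the safety heading, are ticked at day -1 and week 8.

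On the analysis population, Planned data analysis states: "All the efficacy and safety analyses with all randomly assigned participants included will be conducted within the full analysis set (FAS"). A per-protocol analysis is to be run alongside. The primary outcome includes the change in 24-h average systolic and diastolic BP.

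**The concern.** Allocation should be the last step before treatment: first establish that the person qualifies, then measure the baseline, then randomize. Table 2 shows the reverse. A site that works from it would randomize at day -7 and could find at day 0 that the person does not qualify or has not attended.

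Such a person is already randomized and so belongs to the full analysis set. Without a day 0 recording there is no baseline from which to compute a change in 24-h BP. The primary analysis would then carry ineligible people, or people with no computable primary outcome, for a reason that scheduling alone could have avoided.

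**Working it through.** **The plan's own sample size, for reference.** With σ = 10, δ = 4.5, uα = 1.96, uβ = 1.282 and c = 1: n per group = [(1.96 + 1.282) × 10 / 4.5]² × 2 = 103.8, rounded up to 104. The total is 208, and 208 / (1 − 0.20) = 260. This reproduces the stated figure, and nothing in this point changes it.

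**Reading Table 2.** The columns are day -7, day -1, day 0, then weeks 2, 4, 6 and 8. The rows below each have seven cells, so the ticks can be assigned to columns by position.

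| Row of Table 2 | Ticked at |
|---|---|
| Informed consent, medical history | day -7 |
| Allocation | day -7 |
| Routine blood test; liver and kidney function | day -1, week 8 |
| Eligibility screen | day 0 |
| 24-h BP | day 0, week 8 |

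**Gaps from allocation, if Table 2 is followed.**
- To the eligibility screen: 0 − (−7) = 7 days.
- To the baseline 24-h BP: 0 − (−7) = 7 days.
- To the routine blood, liver and kidney tests: −1 − (−7) = 6 days.

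**Text against table.** The text has allocation at day 0 and the table has it at day -7, a difference of 7 days. The text treats the day -7 evaluation as a different visit from the allocation visit, so the two cannot be merged by reading one term loosely.

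**What the text leaves open.** It does not say when eligibility is confirmed. Even with allocation at day 0, Table 2 puts the screen and the 24-h recording on that same day, so the order within the day needs stating.

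**How far the trial had run.** Trial status reports 80 participants recruited and followed to completion at submission: 80 / 260 = 30.8% of the target. It does not say which order they followed.

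**The case against.** The strongest reply is that this is a slip in a table. Eligibility at day 0 with allocation at day -7 reverses any workable order, the text gives a sensible one, and nothing in the prose says that anyone is randomized before screening. The article also cites a full protocol (version 4.0) that is not shown. A slip is indeed the likely explanation. What stands is that the text sends readers to this table for the schedule, the article does not say which version is right, and recruitment was still open.

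Four stronger readings are tempting, and the documents do not support them.

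- *The day -1 laboratory tests decide eligibility, so Table 2 randomizes before eligibility-defining results.* The exclusion criteria cover people "combined with severe primary diseases including liver, kidney, hematopoietic system, nervous system, mental illness, and malignant tumors", to which these tests are relevant. But Table 2 lists them as safety observations, the criterion has no laboratory threshold, and medical history is taken at day -7. Their role in eligibility is an inference. The point rests on the eligibility row itself.
- *The text and table also conflict on the day of the baseline 24-h BP.* The text says: "Blood tests and 24-h BP monitoring will be evaluated only at the enrollment and close-out visits". Taken literally, enrollment is day -7. It may equally mean the whole pre-treatment period, so this conflict is one possible reading only.
- *A day 0 recording is an invalid baseline.* The day 0 column is labelled pre-treatment. In a double-blind trial, a baseline taken after allocation but before the first dose does not by itself favour either arm.
- *About 31% of participants were affected.* That figure is only the share who had completed. The number allocated out of order may be zero.

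It is also fair to say that including everyone randomized is ordinary intention-to-treat practice, that a per-protocol comparison is planned, and that some ineligible or unmeasured participants occur under any schedule. That limits the harm. It does not justify a schedule that invites more of them.

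**Conclusion.** The point holds as an internal contradiction in the current article, with a table that is wrong as printed. Table 2 places allocation 7 days before the eligibility screen and the primary-outcome baseline, and the text places it at day 0.

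The consequence is conditional. If Table 2 was followed, ineligible people or people without a baseline could enter the full analysis set avoidably. If the text was followed, with screening and baseline completed first, the problem does not arise. The documents do not show which happened, so no effect on the result can be given. A reader might infer biased arms or lost power, and neither is supported: the baseline precedes treatment in both arms, treatment is blinded, and the calculation of 260 is untouched.

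The conclusion assumes that the tick marks were extracted in their true columns. The intact seven-cell rows and the plausible placement elsewhere (adverse events, for example, start at week 2) support that.

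**What to change.** In Table 2, move Allocation from day -7 to day 0. Add a footnote that allocation takes place only after (a) eligibility is confirmed, with screening begun in the run-in and the day -1 laboratory results available, and (b) the pre-treatment 24-h BP recording is complete. Swapping the Allocation and eligibility ticks would not be enough, because a screen closed at day -7 would precede the day -1 results.

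Moving the 24-h BP tick to day -1 would be one way to ensure that the recording is finished, but it is optional, since the footnote does the same. If the sentence on blood tests and 24-h BP is edited too, replacing the word enrollment with a single baseline visit would still not match Table 2: the safety blood tests are at day -1 and the cytokines at day 0. Referring to the pre-treatment period would cover both.

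For participants already enrolled, compare the date of allocation with the dates of eligibility confirmation and baseline recording, and report how many, by arm, were allocated and then found ineligible or unmeasured.

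The cost is one tick mark, a footnote and a check of dates that should already be on file. No visit is added, because days -7, -1 and 0 are all in the schedule.
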